### Ethics Approval

The University Institute for Research in Primary Health Care Jordi Gol i Gurina (Barcelona, Spain) ethics committee approved the trial study protocol (approval code: 21/233). Written informed consent will be requested from all parents or legal guardians participating in the study.

## Results

The study is scheduled to begin in January 2022 and is scheduled to end in January 2023, which is when the statistical analysis will begin. As of March 2022, a total of 23 children have been recruited, of which 13 have used VR during the vaccination process. In addition, all of the guardians have found that VR helps to reduce pain during vaccination.

We hope that sufficient evidence can be obtained to demonstrate that the use of VR is effective in reducing anxiety and pain. In this context, the Catalan health system could introduce the use of VR in usual practices and extend its use to other potentially painful processes. Statistically significant differences in heart rate and decreased pain perception that are in favor of the intervention group will be considered a satisfactory result.

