#### Sample Size Determination

To detect a 1-point difference between the two groups on the pain level scale, a sample of 150 boys and girls in each group is required, assuming an SD of 3 points, an α risk of 5%, a power of 80%, and an estimated loss to follow-up rate of 5% [16].

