### Statistical Analysis

An intention-to-treat analysis will be performed; the subjects will be analyzed according to the group to which they were initially assigned and not the group in which they finally participated.

The data will be obtained through Microsoft Forms (an application included in Office 365 [Microsoft Corporation] that allows one to create customized questionnaires, surveys, and records) and analyzed with R software (version 4.0.3) [21,22]. Categorical variables will be described with absolute frequencies and percentages, and continuous variables will be described with means and SDs or medians and quartiles. A 2-tailed *t* test will be used to compare the values related to pain, anxiety, and satisfaction across the two groups. The correlations between pain perception and anxiety values reported by the children and those reported by their caregivers and nurses will be evaluated by means of a Pearson correlation. The significance level will be set at 5%, and all CIs will be set at 95%.

The data will be stored in a database. The Pearson chi-square test will be used for the calculation of statistical significance.

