## Discussion

Our study aims to demonstrate that the use of VR goggles reduces the pain reported by children aged 3 to 6 years during the administration of 2 vaccines. The use of VR goggles may also reduce anxiety after such a procedure and thus result in greater satisfaction among the parents or legal guardians.

There are studies that have already used VR with children for painful procedures and during the administration of vaccines [12-14]. However, to date, there is no literature describing studies that focus on the population of children aged 3 to 6 years who are administered 2 vaccines at the same visit and also record the adverse effects of the use of VR goggles. In this context, our study may provide further support for the use of VR in the management of pediatric patients. Obtaining favorable results could lead to the use of VR as a standard practice for painful procedures performed in the primary care centers of Catalonia. The use of VR for pain reduction is likely to result in a decrease in visit duration. To demonstrate the efficacy of the use of VR, the professionals will note the length (in minutes) of the visits in order to evaluate whether VR reduces or increases the duration of the visits.

Our study has several limitations. The main limitation of the study is the pressure of care and time management in the pediatric consultations conducted by the Well-Child Programme. The time available for caring for a patient is limited. The time required for secluding the participants and obtaining consent and questionnaire data is estimated to be 5 minutes. This means that if the burden of care is high, the quality of care will have to be prioritized, and the recruitment of patients who are eligible to participate in the study will have to be paused.

Another limitation is that parents (or legal guardians) and minors who do not speak Catalan or Spanish cannot participate in the study. The use of VR could be highly advantageous if the VR content is translated into the native languages of these children, because they are usually more fearful and anxious when they cannot understand the pediatrician or nurse.

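### The article's statement of a satisfactory result appears to require heart rate as well as pain, but the 80% power describes pain alone

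*Protocol article*

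**What the plan says.** The only statement of what would count as a favourable outcome is in the Results section of the protocol article: "Statistically significant differences in heart rate and decreased pain perception that are in favor of the intervention group will be considered a satisfactory result".

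Three other places bear on it:

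- *Sample Size Determination* gives the only power statement. The trial is sized "To detect a 1-point difference between the two groups on the pain level scale", "assuming an SD of 3 points", with a 5% α, 80% power and 5% loss, which gives 150 per group. No effect, SD or power is given for heart rate.
- *Discussion* states the aim as pain: "Our study aims to demonstrate that the use of VR goggles reduces the pain reported by children aged 3 to 6 years".
- *Data Collection, Sources of Information, and Intervention* lists heart rate among the outcomes to be compared between groups, with pain, distress and fear, and visit length. *Statistical Analysis* names the two-sided t test as the one that "will be used to compare the values related to pain, anxiety, and satisfaction across the two groups". Heart rate is not in that list.

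**The concern.** If the Results sentence is applied as it reads, a favourable verdict needs two results, and only one of them was planned for. A reader would take the 80% as the chance that the trial reaches its own mark when VR truly lowers pain by 1 point. It is only the chance of passing the pain half. A real pain benefit of the planned size could then be judged unsatisfactory because an outcome with no stated effect, SD or power did not reach significance.

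The sentence can also be read as a list of welcome results, either of which would do. In that case power is not the difficulty. The trial would have two chances of success, each at an unadjusted 5%. Leaving the choice of reading open until the data are in is itself undesirable, particularly as the same paragraph links the outcome to possible adoption of VR by the Catalan health system.

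**Working it through.** **Step 1: reproduce the stated sample size.** Inputs from *Sample Size Determination*: difference 1, SD 3, α 5%, power 80%, loss 5%. The test is two-sided, from *Statistical Analysis*.

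n per group = 2 × (1.960 + 0.842)² × 3² / 1² = 141.3, rounded up to 142.

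Allowing for loss: 142 / 0.95 = 149.5, rounded up to 150. This is the stated figure. (The t-based calculation gives 142.2, and 142.2 / 0.95 = 149.7, again 150.)

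**Step 2: power for pain at the planned evaluable number.**

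Power = Φ[(1/3) × √(142/2) − 1.960] = Φ(0.849) = 80.2%.

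**Step 3: upper limit for both outcomes together.** The event that both tests succeed is contained in the event that the pain test succeeds. So P(both) ≤ P(pain) = 80.2%, whatever is assumed about heart rate.

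**Step 4: size of the loss under assumptions.** The article gives no heart-rate inputs. Let d be the true heart-rate difference in SD units and r the correlation between the two test statistics; both are assumptions. Heart-rate power is Φ[d × √(142/2) − 1.960]. Joint power is the bivariate normal probability that both two-sided 5% tests are significant in favour of VR. At r = 0 it is the simple product, for example 0.802 × 0.392 = 0.314 for d = 0.2.

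| Assumed heart-rate effect | Heart-rate power | Joint power, r = 0 to 0.8 |
|---|---|---|
| 0.20 SD | 39% | 31–39% |
| 0.25 SD | 56% | 45–54% |
| 0.333 SD (as for pain) | 80% | 64–73% |
| 0.40 SD | 92% | 74–79% |
| 0.50 SD | 99% | 79–80% |
| 0.60 SD | 99.9% | about 80% |

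**Step 5: sensitivity to loss.** If all 150 per group were evaluable, pain power would be 82.3%. Joint power would be 68–76% at 0.333 SD, 77–81% at 0.4 SD and about 82% at 0.5 SD.

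**Step 6: cost of requiring both at 80% joint power.** With 0.333 SD on both outcomes, the need is 186 evaluable per group (196 randomised) at r = 0, or 165 evaluable (174 randomised) at r = 0.8, against 150 planned.

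**Step 7: the either-one reading.** With no true effect on either outcome, each two-sided 5% test favours VR falsely with probability 2.5%. If the two tests were independent, the chance of at least one false success in favour of VR would be 1 − 0.975² = 4.9%, about twice the 2.5% for a single test. Positive correlation would make it smaller.

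**The case against.** The strongest reply is that the sentence is not a formal success rule. It stands in Results, not in the sample-size or analysis sections; it closes a paragraph that opens by expressing a hope; and it speaks only of a satisfactory result. Nothing in the article calls heart rate primary or co-primary, or says that the trial fails without it. The grammar is loose too: the requirement of significance may attach to heart rate only or to both outcomes. This much stands, and it limits the point to an inconsistency to be reconciled. It does not remove the point, because no other sentence says what a favourable result would be, and the sentence needs repair under either reading.

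Several stronger readings are tempting but not supported:

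- *That joint power is certainly below 80%.* At 142 per group and a heart-rate effect of 0.6 SD it is about 80%, and with all 150 evaluable and 0.5 SD it is about 82%. What holds is that joint power is never above the pain power.
- *That heart rate is absent from the planned comparisons.* The data-collection section lists it as compared between groups. Only the named test is not stated for it, and a condensed article may leave that to the full protocol.
- *That the error rate is inflated.* Requiring both outcomes does not raise the type I error; its cost is power. The error-rate concern arises only if either outcome suffices.
- *That the sample size is wrong.* It reproduces exactly and matches the aim in the Discussion.

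The success sentence also omits anxiety, although the Abstract's objective includes it. The same paragraph does name anxiety as part of the hoped-for evidence, so little can be built on this.

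**Conclusion.** The concern holds as a mismatch between the criterion in Results and the basis of the sample size. The stated 80% does not describe the chance of meeting that criterion on its natural reading. The firm part, free of assumptions about heart rate, is the ceiling: no more than 80.2% at 142 evaluable per group.

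The shortfall below that ceiling cannot be fixed from the article. It is severe if the heart-rate effect is about 0.2 SD, moderate if it equals the 0.333 SD assumed for pain, and negligible from about 0.5 SD upwards. No single one of these figures should be quoted as the trial's power. This should be fixed. It does not undermine the design, since the sample size and the pain comparison can stay as they are.

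**What to change.** Reword the Results sentence so that the conclusion agrees with the aim and the sample size. For example:

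> The trial's conclusion will rest on the between-group difference in the child-reported Wong-Baker pain score (two-sided 5% level). Heart rate, fear, visit length and satisfaction are secondary and supportive.

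This costs one sentence and no extra children. The downside is that heart rate can no longer carry the headline conclusion.

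If the investigators do intend to require both outcomes, the article should say so plainly, state that the 80% applies to pain only, and report the joint power with the assumed heart-rate effect, SD and correlation. That may show that more children are needed: with equal standardised effects, 174 to 196 randomised per group for 80% joint power.

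The article reports 23 children recruited by March 2022 and analysis starting in January 2023. On that timetable either change can be made before the results are analysed, and it should be recorded and dated accordingly.

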## Discussion

Our study aims to demonstrate that the use of VR goggles reduces the pain reported by children aged 3 to 6 years during the administration of 2 vaccines. The use of VR goggles may also reduce anxiety after such a procedure and thus result in greater satisfaction among the parents or legal guardians.

There are studies that have already used VR with children for painful procedures and during the administration of vaccines [12-14]. However, to date, there is no literature describing studies that focus on the population of children aged 3 to 6 years who are administered 2 vaccines at the same visit and also record the adverse effects of the use of VR goggles. In this context, our study may provide further support for the use of VR in the management of pediatric patients. Obtaining favorable results could lead to the use of VR as a standard practice for painful procedures performed in the primary care centers of Catalonia. The use of VR for pain reduction is likely to result in a decrease in visit duration. To demonstrate the efficacy of the use of VR, the professionals will note the length (in minutes) of the visits in order to evaluate whether VR reduces or increases the duration of the visits.

Our study has several limitations. The main limitation of the study is the pressure of care and time management in the pediatric consultations conducted by the Well-Child Programme. The time available for caring for a patient is limited. The time required for secluding the participants and obtaining consent and questionnaire data is estimated to be 5 minutes. This means that if the burden of care is high, the quality of care will have to be prioritized, and the recruitment of patients who are eligible to participate in the study will have to be paused.

Another limitation is that parents (or legal guardians) and minors who do not speak Catalan or Spanish cannot participate in the study. The use of VR could be highly advantageous if the VR content is translated into the native languages of these children, because they are usually more fearful and anxious when they cannot understand the pediatrician or nurse.

There are other limitations associated with the study design, patient recruitment, and the inclusion and exclusion criteria. First, patients receiving vaccines from their private pediatricians will be excluded. Second, the study population will be limited to a specific age range. Third, evaluations will only be conducted for vaccination and not for other invasive procedures. Fourth, patients who have already received 1 of the 2 scheduled vaccines will be excluded, since they would have previously presented the related pathology (eg, patients who have already been vaccinated for chickenpox). Fifth, parents or legal guardians who do not agree with vaccination in general or are associated with the masking process may introduce bias when they report their experiences in the survey.

## Abbreviations

VR: virtual reality
